### Participants

The aim is to recruit 100 participants in total for this feasibility study, 50 intervention participants and 50 control participants to allow for comparison at the 3-month follow-up point and 6-month exit point. We will recruit males and females aged 16 +.

*Inclusion criteria:* Participants will be willing to take up the offer of LL and appropriate for usual Remploy support—and with no active risk to self at initial Remploy assessment (this is not routinely investigated, but if suicidality is disclosed at the initial assessment, the individual will not enter the study). Individuals must be able to register on the website, read and understand the LL resources via the internet or DVD; at home or in the Remploy office.

*Exclusion criteria:* Individuals will be excluded if they are unwilling or unable to use the LL approach and/or if they are at active risk of suicide, identified in which case usual care (referral to GP) will occur as is normal Remploy practice.

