### Procedure for recruitment and study setting

All new candidates will be informed of the study, and their Remploy case loader (support worker) will provide a study information pack and consent form. The potential participant will be asked to bring the consent form to their meeting the following week if they wish to take part in the study. The researcher’s contact details will be on the information sheets to allow candidates to ask questions about the study (meaning the consent given will be informed consent). The Remploy staff can also answer any questions required. Taking up or declining the study will not affect the usual support received.

On attendance at the Remploy Office for the second appointment, completed consent forms will be collected by administration staff. Participants will then hand in their baseline questionnaires to the administration staff. The administration staff will mark up the participants’ case notes as being in the study and pass a treatment allocation envelope to the case loader. The sealed allocation envelopes will have been prepared remotely by the researcher and will be selected in the presence of the participant from a box to reveal the group allocation. Envelopes will state which course they have been enrolled in (1—immediate, 2—delayed). Those allocated to the LL group will be given details of how to access the online resources. Participants will work through the online modules in the Remploy offices either on their own or as part of a group with a trained Remploy facilitator, the delivery type for each participant will be recorded by Remploy. It will not be possible for the caseloader, participant or researcher to be blind to the group allocation.

All participants will receive supportive encouragement from a trained member of staff while they use the intervention. TAU participants will be given access to Living Life after the 3 month follow-up data has been collected. The “Living Life” intervention is password protected. However, in order to identify contamination at the 3-month follow-up, participants will be asked to detail any support they have received for their mood since entering the study.

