#### Consent

After expressing an interest in the study, potential participants will be asked to complete an eligibility pack, which will include a participant information sheet along with a consent form. Participants will have the opportunity to ask questions about the study by phone, email or post before being asked to complete the consent form. Until eligibility has been assessed and informed consent has been given, individuals will not be able to begin participation in the study.

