#### Confidentiality

Data collected by Remploy will be kept and stored in accordance with their usual internal procedures. Data collected by the research team will be kept either on fingerprint or password-locked memory sticks, on fingerprint identification laptops, stored in a locked filing cabinet in the researcher’s office on the site of Gartnavel Royal Hospital, or will be saved on a secure network space that only the researchers have access to. Personally identifying information will be removed from the main electronic data files for analysis by the researchers at the Robertson Centre for Biostatistics, University of Glasgow. A coded file with sensitive data will be stored separately.

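### Active suicide risk is an exclusion that rests on volunteered disclosure at the first meeting, and the described route from hand-in of the baseline PHQ-9 to allocation has no step that reads it

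*Protocol article*

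**What the plan says.** The Participants section requires that there be no active risk to self at the initial Remploy assessment. It says of this risk: "this is not routinely investigated, but if suicidality is disclosed at the initial assessment, the individual will not enter the study". The exclusion criteria add that people are excluded "if they are at active risk of suicide, identified in which case usual care (referral to GP) will occur as is normal Remploy practice".

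The order of events is given under Procedure for recruitment and study setting. At the first contact, "their Remploy case loader (support worker) will provide a study information pack and consent form". At the second appointment, administration staff collect the consent forms. Then: "Participants will then hand in their baseline questionnaires to the administration staff". The same staff mark the case notes to show study entry and "pass a treatment allocation envelope to the case loader". The envelopes "will be selected in the presence of the participant from a box to reveal the group allocation".

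Baseline data collection lists the PHQ-9 among the baseline measures. The PHQ-9 section describes nine items built on the DSM-IV criteria for depression, each scored 0 to 3, but does not list them.

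Three other places bear on the point:

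- Consent states: "Until eligibility has been assessed and informed consent has been given, individuals will not be able to begin participation in the study".
- Benefits to participants sends deterioration to usual Remploy guidelines and makes two team members available for consultation.
- Collaboration with Remploy says that case workers can help anyone who needs more support.

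**The concern.** The trial sets a safety exclusion and, by its own account, does not routinely look for the condition. It then collects a depression questionnaire just before allocation and describes no use of it for that exclusion.

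The population makes this relevant. Aims includes people with clinically diagnosed major depression, and Participants sets no upper limit on the PHQ-9 score. The Discussion hopes to reach people who might not engage with NHS services, so some entrants may have no clinician asking about risk.

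What is at stake is a missed exclusion and a missed prompt for GP referral. No estimate, test or feasibility threshold is affected.

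**Working it through.** The main check is a reading of the text; only the workload of the remedy needs arithmetic.

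**Is there a trigger before allocation?**

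| Section | What it supplies | What it leaves open |
|---|---|---|
| Participants | The exclusion, GP referral if risk is identified, and ascertainment by disclosure at the first meeting | Any enquiry beyond volunteered disclosure |
| Procedure for recruitment and study setting | Consent forms collected, questionnaires handed in, notes marked, envelope passed on, envelope selected | Anyone reading the questionnaires |
| Consent | Eligibility must be assessed before participation | Who assesses it, how, and whether risk or the PHQ-9 is looked at |
| Benefits to participants | A response to deterioration, and a consultation route | What sets it off when risk is already present at baseline |
| Collaboration with Remploy | Case-worker help for those who need it | The same trigger |
| Trial status | Case workers briefed on protocol and recruitment, and trained in support sessions | Any mention of risk |

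The response routes exist. The only stated means of detection is disclosure at the first meeting, and the form that could prompt a second look arrives at the next appointment.

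**Does the form carry the information?** The article says the nine items mirror the DSM-IV depression criteria. That implies an item on self-harm or suicidal thoughts but does not show it, so this is an inference.

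**Workload of a baseline check.** Inputs: 100 participants planned (Participants), 20 already entered (Trial status), and a target of 3–4 per week for 6 months (Determining the feasibility of the study design).

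- Target rate, taking 6 months as 26 weeks: 3 × 26 = 78 and 4 × 26 = 104, consistent with the planned 100.
- Baseline forms still to come: 100 − 20 = 80.
- Time to collect them at the target rate: 80 / 4 = 20 weeks to 80 / 3 = 26.7 weeks, which is 3–4 one-item checks per week.

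**Largest effect of under-reporting confined to that item.** One item contributes at most 3 of the 27 PHQ-9 points: 3 / 27 = 11%.

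These figures size the remedy. The article gives no rate of undisclosed risk, and none is assumed here.

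**The case against.** The strongest reply is that this argues from silence in a condensed article. Who reads which form, and what happens next, is often left to the full protocol or site procedures. The recruitment narrative is also visibly incomplete: Consent promises an eligibility assessment that does not appear among the second-appointment steps. Relying on the service's usual practice is openly stated in a low-intensity study run inside an employment service. Case-worker contact is weekly or fortnightly, and the exclusion criterion as worded covers any risk that is identified.

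Part of this stands. A fuller document may hold a check, and the narrative does not prove that nobody looks. But the article does more than omit a step. It states how risk is ascertained, says that it is not routinely investigated, and sets out the sequence up to allocation. No other section supplies a trigger, so the baseline point survives.

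Four stronger readings are tempting and are not supported:

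- **That the protocol contradicts itself.** It does not: risk identified before allocation already excludes.
- **That people at risk are denied care.** Overview gives both arms treatment as usual.
- **That risk shown on the 3- and 6-month forms is mishandled.** The article is merely silent on this, articles commonly leave it to the full protocol, and Benefits to participants partly covers it.
- **That a positive answer is itself active risk.** It is a reason to ask.

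**Conclusion.** The point holds for the baseline step only. Active suicide risk is an exclusion whose sole stated means of detection is volunteered disclosure at the first meeting, and the described sequence passes from the completed PHQ-9 to allocation without a reading of it. Someone who stays silent at the first meeting and indicates risk on the form can be randomised without the exclusion or referral being considered.

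The number of people affected is unknown. With 20 of 100 entered when the article was written, up to 80 entrants could still pass through an amended procedure; that is the reach of a change, not an estimate of people at risk.

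The conclusion assumes that the PHQ-9 as used includes the implied self-harm item and that no fuller document already places a check before allocation. A check helps only those who mark the item. This is a worthwhile, inexpensive safety improvement and does not bear on the validity of the analysis.

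**What to change.** In Procedure for recruitment and study setting, add one step after the baseline questionnaires are handed in and before the envelope is selected:

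1. An already briefed case worker checks the PHQ-9 response on self-harm, and no other item.
2. A positive response leads to a private conversation. If the case worker is unsure, the consultation route in Benefits to participants is used. Allocation waits until the question is settled.
3. If active risk is confirmed, the person is excluded and the GP referral already in the exclusion criteria is made.
4. The information pack says that this item will be looked at, and by which role.

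Because the check comes before the sealed envelope is selected, it cannot depend on the allocated arm. The randomisation method and the analysis are unchanged. If a fuller document already contains such a step, one sentence pointing to it is enough.

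Costs and downsides:

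- A short addition to the case workers' briefing, including a clear rule for when to consult, since they are not clinicians.
- About 3–4 checks a week at the target recruitment rate, which is a target and not an observed rate.
- An occasional delayed allocation or exclusion.
- Confidentiality: one Remploy role sees one sensitive answer. The Confidentiality section sets separate rules for research data, while "Data collected by Remploy will be kept and stored in accordance with their usual internal procedures". Limiting the check to one item and one role keeps this small.
- Candour: some people may under-report on that item, by at most 3 of 27 points if it stops there. Wider loss of candour cannot be sized from the article.
- The added sentence in the information pack may need sign-off from the ethics committee.

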### Procedure for recruitment and study setting

All new candidates will be informed of the study, and their Remploy case loader (support worker) will provide a study information pack and consent form. The potential participant will be asked to bring the consent form to their meeting the following week if they wish to take part in the study. The researcher’s contact details will be on the information sheets to allow candidates to ask questions about the study (meaning the consent given will be informed consent). The Remploy staff can also answer any questions required. Taking up or declining the study will not affect the usual support received.

On attendance at the Remploy Office for the second appointment, completed consent forms will be collected by administration staff. Participants will then hand in their baseline questionnaires to the administration staff. The administration staff will mark up the participants’ case notes as being in the study and pass a treatment allocation envelope to the case loader. The sealed allocation envelopes will have been prepared remotely by the researcher and will be selected in the presence of the participant from a box to reveal the group allocation. Envelopes will state which course they have been enrolled in (1—immediate, 2—delayed). Those allocated to the LL group will be given details of how to access the online resources. Participants will work through the online modules in the Remploy offices either on their own or as part of a group with a trained Remploy facilitator, the delivery type for each participant will be recorded by Remploy. It will not be possible for the caseloader, participant or researcher to be blind to the group allocation.

All participants will receive supportive encouragement from a trained member of staff while they use the intervention. TAU participants will be given access to Living Life after the 3 month follow-up data has been collected. The “Living Life” intervention is password protected. However, in order to identify contamination at the 3-month follow-up, participants will be asked to detail any support they have received for their mood since entering the study.

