## Methods/design

### Overview

This is a feasibility study to test the possibility of delivering the Living Life (LL) online life skills resource in Remploy. In this RCT, 50% of participants will be randomly allocated to the immediate group (IA) and will receive LL immediately. The remaining 50% of participants will be allocated to the delayed access control (DAC) group. Both arms receive treatment as usual. The primary end point is 3 months at which point the control arm will be provided with access to LL if they wish. Monitoring will continue up to a 6-month final exit point.

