## Trial status

Ethical approval has been granted by the College of Medical, Veterinary & Life Sciences Ethics Committee for Non Clinical Research Involving Human Subjects, University of Glasgow, Ref. 2012063. The case workers at the Remploy offices in Edinburgh and Hamilton have been briefed on the study protocol and recruitment process and have undergone training on how to deliver the support sessions to participants. Recruitment is ongoing; to date, 20 participants have entered the study.

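### Envelopes are picked from a box in no set order, so a discarded or repeated draw is neither prevented nor detectable from the procedure described

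*Protocol article*

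**What the plan says.** The allocation steps are in the protocol article under Procedure for recruitment and study setting. At the second appointment, administration staff collect the consent forms and participants hand in their baseline questionnaires. The staff then mark the participant's "case notes as being in the study" and "pass a treatment allocation envelope to the case loader".

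The next sentence describes the envelopes. "The sealed allocation envelopes will have been prepared remotely by the researcher", and they "will be selected in the presence of the participant from a box to reveal the group allocation". After opening, there is no blinding: "It will not be possible for the caseloader, participant or researcher to be blind to the group allocation".

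Other sections give the setting:

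- Overview: "50% of participants will be randomly allocated to the immediate group (IA) and will receive LL immediately", with the rest in the delayed arm.
- Participants: "The aim is to recruit 100 participants in total for this feasibility study, 50 intervention participants and 50 control participants". Eligibility requires willingness to take up the Living Life package.
- Research questions: the primary question asks, among other things, whether participants can be randomised.
- Trial status: "The case workers at the Remploy offices in Edinburgh and Hamilton have been briefed on the study protocol and recruitment process". Twenty participants have entered so far.

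**The concern.** Sealed envelopes protect allocation best when the next participant must receive the next envelope. Picking from a box removes that link. If the first pick is unwelcome, or is put back before opening, a second pick leaves no gap in any sequence.

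There is a plausible pull towards one arm. Everyone eligible is willing to use the package, and controls wait 3 months for it. The envelope also passes through a case loader who will work with the participant in the following weeks. The participant's presence discourages tampering by staff, but a participant who hoped for immediate access would have little reason to object to a second pick.

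Two things are at stake. The between-arm comparison of mood and social function rests on questionnaires with no blinding, and those data feed the sample size for the later trial. The study is also meant to show that randomisation works in this service, and a procedure whose integrity cannot be demonstrated shows that only weakly.

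**Working it through.** The article states no figure that depends on the allocation method, so there is none to reproduce. The check compares the stated steps and adds two illustrations.

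**1. What each stated step protects against**

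| Stated step | Protects against | Leaves open |
|---|---|---|
| Consent, baseline and case-note marking come first | Selective entry once the arm is known | A second pick after entry |
| Sealed and prepared remotely | Foreknowledge of contents (opacity is not stated) | A second pick after opening |
| Participant present | A covert swap by staff | A second pick that the participant welcomes |
| Selected from a box | – | No fixed link between participant and envelope |

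One sentence has administration staff hand over a single envelope. The next has an envelope selected from a box, with no subject for the verb. The two can describe one event, so this is an ambiguity about who selects, not a contradiction.

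**2. Would arm totals reveal redraws?**

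Assume that a share r of unwanted draws is redrawn once, that each draw is 50:50, and that all redraws favour the same arm. Then P(preferred arm) = 0.5 + 0.5 × r × 0.5 = 0.5 + 0.25r. The article gives no value of r, so a range is shown.

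| r (assumed) | P(preferred arm) | Expected number of 100 |
|---|---|---|
| 5% | 0.5125 | 51.25 |
| 10% | 0.525 | 52.5 |
| 20% | 0.55 | 55 |

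With independent 50:50 draws, the SD of the count among 100 is √(100 × 0.5 × 0.5) = 5. Even r = 20% shifts the total by only one SD, and redraws in opposite directions would cancel. A balance check is therefore a poor detector. An ordered, reconciled log is a better one.

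**3. Does office balance add to the problem?**

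The article names two offices but does not say what the box holds or whether each office has its own. The table takes three assumed set-ups and assumed office sizes. It gives the 2.5th to 97.5th percentile range for one arm and, in brackets, the chance of a 60:40 split or worse.

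| Office size | Shared box of 50+50 (hypergeometric) | Independent 50:50 (binomial) | Own box of 25+25 |
|---|---|---|---|
| 50 | 20–30 (7%) | 18–32 (20%) | exactly 25:25 |
| 30 | 11–19 (28%) | 10–20 (36%) | 12–18 (15%) |
| 20 | 6–14 (45%) | 6–14 (50%) | 7–13 (39%) |

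The answer depends on the unstated contents. The cost is small in any case: relative information at a 60:40 split is 4 × 0.6 × 0.4 = 0.96, a loss of 4%. The issue is selection, not precision.

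**The case against.** The strongest reply is that the stated safeguards do most of the work. Entry is fixed before the arm is known, the contents are sealed and prepared off site, and a redraw after opening would have to happen in front of the participant. That stands, and it makes the remaining gap narrow. It does not close it, because none of these steps fixes which envelope is used.

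A second reply is that a journal article condenses a fuller protocol, which may hold numbering or a log. For the log this is fair. For the order of use it is weaker: the article positively describes selection from a box, and numbered envelopes used in strict order would be a different procedure.

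Four stronger readings are tempting but not supported:

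- *The case loader knows the allocation beforehand.* The no-blinding sentence describes the position once the arm is revealed. Nothing says that the contents are known earlier.
- *There is no audit trail.* The article describes none, but study entry is recorded in the case notes, and silence in a condensed article does not show that none exists.
- *Balance within offices is unprotected.* This holds for a shared box or independent assignment. It fails for a separate balanced box per office that is used up.
- *The bias has a calculable size.* Assuming that 10% of each arm is steered, with a 0.5 SD prognostic difference in opposite directions, gives 0.1 × 0.5 + 0.1 × 0.5 = 0.10 SD, against a standard error of √(2/50) = 0.20 SD. Neither input has a source in the document. Under the single-redraw model, moving 10% of participants needs 0.25r = 0.10, so r = 40%, which is a great deal of redrawing with participants watching.

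Finally, the section on determining feasibility judges recruitment, adherence, acceptability and follow-up, and none of these depends much on who draws. That limits the weight of the point. The primary research question nevertheless names randomisation explicitly.

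**Conclusion.** The point holds in a limited form. The method described is an unordered pick at the office, with the person selecting left unclear and the envelope passing through the case loader. A discarded or repeated draw is neither prevented nor detectable from that description. The sealed, remotely prepared envelopes and the timing after consent and baseline reduce the risk of foreknowledge and selective entry, but not of redrawing.

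No bias estimate is possible. The redraw shares of 5% to 20% are assumptions, used only to show that plausible redrawing would not stand out in arm totals. Office imbalance is not part of the conclusion. The point bears mainly on the unblinded mood and function comparison and on what the study can claim about the feasibility of randomising in this service. It is worth acting on because the remedy is cheap and, with 20 of 100 entered, 100 − 20 = 80 participants could still be covered.

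**What to change.** For the remaining participants, replace the pick from a box as follows:

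- Prepare sequentially numbered, opaque, sealed envelopes remotely from a computer-generated list.
- Have administration staff hold them and use them strictly in numerical order.
- Once consent and baseline questionnaires are in, write the participant ID and date on the next envelope before it is opened.
- Keep a log of envelope number, ID and date, and have the researcher reconcile it against entered participants and unused envelopes.
- State who opens the envelope.

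A separate numbered sequence for each of the two offices is a practical option, since each office then holds its own stock. Blocking, formal stratification and an office term in the model are optional in a study of this size. Short blocks could also make later allocations easier to guess where staff know every arm.

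The cost is a new list, relabelled envelopes and a little administrative work in a study that describes itself as unfunded. The drawback is that the procedure will differ from that used for the first 20 participants, so the report should say when it changed and how many were allocated under each method. The change does nothing about the lack of blinding after allocation, which is a separate limitation.
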